## Abstract

**Background::**

South Korea has a dual medical system comprising conventional Western medicine (WM) and traditional Korean medicine (KM), which has yielded both positive results (increased opportunity to choose medical care) and negative results (increased medical costs). Thus, the Ministry of Health and Welfare has been performing a pilot project to evaluate this collaborative system in the real clinical situation. As treatment of dementia requires a social approach, the Korean government aims to strengthen the role of the national health care system to reduce the burden of dementia. The aim of this study was to evaluate the clinical - and cost-effectiveness of collaborative KM and WM treatment in patients with dementia or mild cognitive impairment (MCI) in Korea.

**Method/design::**

In total, 180 patients with dementia or MCI will be recruited and will undergo monthly check-up for 12 weeks. Information regarding demographic characteristics, baseline disease-related data, and outcomes related to cognitive function and quality of life will be obtained. For data analysis, the patients will be classified into 2 groups using a comparative observational study design: the sole treatment group, which will receive either WM or KM alone, and the collaborative treatment group, which will receive both WM and KM.

**Discussion::**

The treatment of dementia/MCI in South Korea will be studied in the real world during the pilot project. There will be no limitations on the type of treatment or the specific treatment method. Examining the clinical- and cost- effectiveness of the different methods will supply information for building an optimal medical system for the treatment of dementia/MCI.

**Trial registration::**

The protocol for this study has been registered at the clinical research information service (CRIS: KCT0002868).

## Introduction

1

The Republic of Korea has a dualized medical system, established in 1951, which consists of Western medicine (WM) and Korean medicine (KM). The dualized system increases the opportunity for each patient to choose the medical care that he or she hopes to receive and helps to preserve traditional knowledge. However, it has some negative aspects, such as conflicts between practitioners of the 2 systems, and duplicated medical use.^[1]^ Academic studies and institutional discussions have been carried out to address these issues, and the necessity of collaborative treatment wherein WM and KM exist in an independent system and are used cooperatively has been suggested.^[2]^

Factors hindering collaborative treatment include lack of experience and knowledge of practitioners of one system regarding the other system^[3–5]^ and the limitations of the regulatory and legal systems, including the National Health Insurance System (NHIS).^[3,6–8]^ The NHIS of Korea currently covers only the cost of previous care if patients receive both WM and KM for the same disease in the same day. As this practice was recognized as an obstacle to collaborative treatment, the Korean government conducted a “first-stage pilot project of KM-WM collaborative treatments,” which also covered the cost of subsequent treatment by the NHIS.^[9]^ This pilot project yielded positive results, such as increased doctor and patient satisfaction and a decrease in the length of treatment.^[10]^ This initial pilot project was followed by “the second-stage pilot project of KM-WM collaborative treatments,” which is ongoing since November 2017. The second-stage pilot project emphasizes cooperation and consultation between medical doctors and Korean medical doctors (KMDs) according to an optimized protocol for each disease. It also allows for additional costs called “WM-KM consultation fees” for diseases that were frequently observed in the first-stage pilot project or considered important diseases in Korea based on prevalence and mortality.

Prevention, early detection, active treatment, and long-term management including social support are important in the treatment of dementia,^[11]^ which is one of the “4 major diseases” in South Korea.^[12]^ The Korean government is aiming to strengthen the national approach to dementia using programs such as the “national responsibility for dementia care.”^[13,14]^ Mild cognitive impairment (MCI) is an intermediate condition between normal aging and the initial state of dementia. In this condition, the degree of deterioration of cognitive function is mild and there are no deficits in the ability to perform activities of daily living (ADL). MCI is also recognized as a predictor of future progression to dementia.^[15,16]^ Previous studies have reported the effectiveness of KM treatment for cognitive dysfunction,^[17–19]^ and KM treatments are widely used in South Korea for treatment of cognitive impairment.^[20]^

We would like to determine whether collaborative treatment of dementia/MCI using both WM and KM is more effective and cost-effective than treatment using either WM or KM. We have designed a prospective, multicenter, observational study investigating cognitive function, quality of life (QoL), and medical use parameters such as cost and duration.

## Methods and design

2

### Study design and setting

2.1

A multicenter, outpatient department (OPD)-based, prospective observational study of patients diagnosed with MCI or dementia is being conducted from April 2018 to December 2018, as a part of a Registry for Korean Medicine and Western Medicine Collaborative Treatment (REKOMENT study). Participants are recruited from 6 university-affiliated hospitals and 1 national medical center, which are participating in the “second-stage pilot project of KM-WM collaborative treatments.” The participants receive treatments from practitioners of KM and/or WM as they would in the real world, and are asked to undergo additional assessments. We will analyze the type of treatment (collaborative or sole treatment), changes in assessment scores, and costs for treatment of MCI/dementia. A comparative observational study design has been adopted to compare the participants in a collaborative treatment (CT) group and those in a sole treatment (ST) group. The study flowchart can be found in the flow diagram (Fig. 1).

**Figure 1 F1:**
[figure not shown]
Flow diagram. f/u = followup, KM = Korean medicine, MCI = mild cognitive impairment, WM = Western medicine.

### Participants

2.2

#### Inclusion criteria

2.2.1

Adult patients from institutions participating in the “second-stage pilot project of KM-WM collaborative treatment” whose main diagnosis is MCI or dementia (10th revision of the International Statistical Classification of Diseases and Related Health Problems F00, F01, F02, F03, F067, G30, or G31) aged 75 years or younger.Patients whose global Clinical Dementia Rating (CDR) score is between 0.5 and 2.0 (0.5 ≤ CDR ≤ 2.0).Patients who decide to participate in the study by their own voluntary will (or that of a legal representative when the patient has limited ability to agree, but can still express willingness to participate) and submit written consent.

#### Exclusion criteria

2.2.2

Patients who are currently participating in another clinical trialPatients who have difficulties in participating in the study, as judged by the researchers, such asThose who are expected to have difficulty in complying with the study schedule.Those who are expected to have difficulty understanding and responding to the study questionnaires, such as those who are illiterate or those with serious health conditions (e.g., unstable vital signs).

### Consent and registration

2.3

The subjects are recruited from the OPDs of 7 of the hospitals participating in the pilot project. Independent researchers who are not in charge of the treatment of the subjects inquire regarding the willingness of the subjects to participate in this observational study. The researchers provide the potential subjects with detailed written information regarding the study and provide them with the opportunity to ask questions regarding the study. The researchers emphasize that the patient's participation in this study will not have any effect on his or her treatment. When a subject finally decides to participate in this observational study, he or she will be asked to submit written informed consent. For patients with a limited ability to consent, an explanation of the study will be provided to both the patient and the patient's legal representative and written consent will be obtained from both individuals. In this case, the study will proceed to the next step only when the patient certainly expresses his/her willingness to participate.

After providing written consent, the subjects will be screened for the eligibility criteria. When a subject is judged suitable for participation in the study, he or she will be registered for the study and assigned a registration number.

### Data sources, measurements, and management

2.4

Data regarding effectiveness will be collected using participant surveys and clinical evaluations. Data regarding costs will be obtained using participant surveys, administrative data from each institution, and Health Insurance Review and Assessment (HIRA) data.

The participant survey includes information regarding demographic characteristics, medical history, use of long-term care services, and costs for the MCI/dementia treatments. The demographic information obtained includes date of birth, sex, level of education, and occupation (current or past). The medical history information collected includes treatment history, other diseases that the patient has, history of drinking and smoking, and family history.

The Korean Medical Pattern Identification for Dementia (KPD) score will be used to assess pattern identification in each patient.^[21]^ Pattern identification is also known as syndrome diagnosis, and is a major method used to classify symptoms. It is broadly used in traditional Chinese medicine and KM. Information regarding long-term care services will also be obtained, including the score of long-term care insurance service and the contents of long-term care service currently in use. Direct medical costs and direct nonmedical costs of the MCI/dementia treatments will be assessed using surveys of patients or their guardians based on the “limited societal perspective.”^[22]^

The clinical evaluation includes: assessment of the severity of MCI/dementia using measures such as the CDR,^[16]^ Global Deterioration Scale (GDS),^[23]^ Mini-Mental State Exam (MMSE),^[24]^ Korean Montreal Cognitive Assessment (MoCA-K),^[25]^ and Short-Form Geriatric Depression Scale (S-GDpS);^[26]^ and 2) assessment of QoL using measures such as the Seoul Instrumental Activities of Daily Living (S-IADL),^[27]^ Neuropsychiatric Inventory-Questionnaire (NPI-Q),^[28]^ Barthel Activities of Daily Living (Barthel-ADL),^[29]^ EuroQoL-5 Dimension (EQ-5D),^[30]^ and EuroQol-visual analog scale (EQ-VAS).^[31]^

Appropriate standardization procedures have been implemented to minimize differences between evaluators in the different institutions as much as possible. KM or WM physicians with >1 year of clinical experience are in charge of the clinical evaluations. The QoL assessment is based on responses of patients or their guardians to a questionnaire. The patients and/or guardians are allowed to ask the researcher questions if there are difficulties in understanding the meaning of a question. However, they are required to respond to the questions independently without intervention from the researchers.

Administrative data from each institution will be used to determine the costs of MCI/dementia treatments, and the type and frequency of collaborative treatment. Data obtained from the HIRA include medical expenses of the patients, the duration of medical use, and the type of medical services used by the patients.

The time schedule for data collection is presented in Table 1. All collected data will be recorded using iCReaT, which is a type of electronic case report form supplied by the Korea National Institute of Health. The study procedures including the data collection and management will be monitored by the Monitoring Center for Korean Medicine and Western Medicine Collaboration, which is governed by the Ministry of Health and Welfare.

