##### Cognitive function

2.5.1.2

Changes in the MoCA-K, MMSE, CDR, and GDS scores from baseline to 8 weeks will be used to evaluate effectiveness in terms of improvement in cognitive function.

The MoCA was created to screen for individuals with MCI, who have normal scores on the MMSE. The questionnaire consists of visuospatial/executive ability, naming, memory, attention, language, abstraction, delayed recall, and orientation domains.^[34]^ The MoCA-K, which is a validated Korean version of the test,^[25]^ is used in this study. We have registered the study on *mocatest.org*.

The MMSE is one of the most broadly used screening tests for dementia. It was created by Folstein et al and can be completed in 5 to 15 minutes. This test has a total score of 30. It has the advantage of being useful in assessing changes over time, based on repeated measures during disease progression. This is because the test only has a small learning effect.^[35]^ The reliability and validity of the MMSE have been demonstrated in distinguishing moderate and severe dementia.^[24]^ The official Korean version of the test, which is supplied by the Psychological Assessment Resources, is used here.

The CDR is the most widely used test to evaluate the severity of dementia. It is divided into the following domains: memory, orientation, judgment and problem-solving, community affairs, home and hobbies, and personal care. Each category is scored on a 5-point severity scale (none, questionable, mild, moderate, and severe).^[36]^ The Korean CDR has been shown to be valid.^[16]^ The score is determined by the doctor, who makes his or her assessment based on detailed examinations of the patient and his or her caregiver.

The GDS is used to evaluate overall cognitive function. It is scored on a scale of 1 to 7 (0, no cognitive decline; 2, very mild cognitive decline; 3, mild cognitive decline; 4, moderate cognitive decline; 5, moderately severe cognitive decline; 6, severe cognitive decline; and 7, very severe cognitive decline).^[37–39]^ The validity of the Korean version of the GDS has been demonstrated.^[23]^

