### Treatments

2.6

The participants receive treatment for MCI/dementia, mostly based on their practitioners’ clinical opinions; thus, there is no fixed treatment for the study. The participants can freely choose any type of WM and/or KM treatment method. When a participant wishes to receive both WM and KM treatment, the practitioner of 1 type of medicine used for the patient's treatment will make a “request for a collaborative treatment” to a practitioner of the other type of medicine. The participants can freely decide the type of treatment in consultation with their practitioners at any time, as with general care. All treatments that the participants receive will be recorded and monitored.

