### Statistical and analytical plans

2.8

Baseline characteristics and disease progression will be compared between the CT and ST groups. All continuous variables will be tested to confirm normality. Student *t* tests or Wilcoxon rank sum tests will then be used to compare the means of the 2 groups. Categorical data will be analyzed using *χ*^2^ or Fisher exact tests. Per-protocol and intention-to-treat (ITT) analyses will be used to assess all effectiveness and cost-effectiveness data. Missing volume, pattern, and mechanisms will be analyzed before the ITT analysis. If the missing mechanism is identified as missing completely at random or missing at random, as defined by Rubin,^[43]^ the multiple imputation method will be used to replicate the missing data. Scores on the S-IADL, Barthel-ADL, S-GDpS, NPI-Q, MoCA-K, MMSE, CDR, GDS, and QoL as measured by the EQ-5D and EQ-VAS, and the use of long-term care service will be compared between the 2 groups for effectiveness analysis. Means and 95% confidence intervals for continuous variables and frequencies and percentages for categorical variables will also be calculated. All statistical analyses will be performed using 2-tailed tests at a significance level of .05. In the economic evaluation, the ICER results will be analyzed deterministically using mean values, and the statistical significance of differences in ICER will be determined using the bootstrapping method. CEAC will also be analyzed and reported along with the meaningful ranges for the national thresholds. Stata MP version 14 (StataCorp LLC, TX) and SAS version 9.4 (SAS Institute Inc., Cary, NC) will be used for all of the aformentioned analyses.

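### If time on treatment before registration differs between the collaborative and sole groups, the unadjusted comparison of 4- and 8-week change is confounded by it

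*Protocol article*

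**What the plan says.** **Entry.** Section 2.2.1 of the protocol article admits adults up to age 75 "whose main diagnosis is MCI or dementia" with a global CDR of 0.5 to 2.0. The exclusions in 2.2.2 concern other trials and difficulty in taking part. Neither list mentions previous or current WM or KM treatment.

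**Source and time zero.** Section 2.3 states: "The subjects are recruited from the OPDs of 7 of the hospitals participating in the pilot project". After consent and screening, an eligible patient enters the study: "he or she will be registered for the study and assigned a registration number". Nothing ties this date to the start of any treatment.

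**Treatment.** Section 2.6: "The participants can freely decide the type of treatment in consultation with their practitioners at any time". Collaboration begins when a practitioner of one system sends a request to a practitioner of the other.

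**Outcomes.** The quality-of-life outcomes in 2.5.1.1 are changes from baseline to weeks 4 and 8. The cognitive outcomes in 2.5.1.2 are "Changes in the MoCA-K, MMSE, CDR, and GDS scores from baseline to 8 weeks".

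**Data on prior care.** Section 2.4: "The medical history information collected includes treatment history". The same section lists, among the HIRA data, "the duration of medical use, and the type of medical services used by the patients".

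**Comparison.** Section 2.8 names Student t tests or rank tests for continuous variables: "Wilcoxon rank sum tests will then be used to compare the means of the 2 groups". Categorical data get chi-square or Fisher tests. It names no covariate, stratum, matching or weight. Baseline characteristics are to be compared between the groups.

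**The concern.** A change score over 4 or 8 weeks means different things at different points in a course of treatment. A new starter may show an early response inside the window. In a patient treated for a long time, that response came before registration and is not measured.

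The groups are self-selected, so nothing in the design makes them alike in how long they had been treated before registration. If they differ, part of the CT-ST difference reflects time already on treatment and not collaboration. It could go either way. Many long-standing users of both systems in CT would pull the contrast against CT, while many long-standing single-system users in ST would pull it towards CT.

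At stake is the study's stated question, whether collaborative treatment does better than either system alone.

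**Working it through.** **1. The plan's own figure.** Section 2.7 wants 120 complete cases with 20% missing: 120 / (1 - 0.20) = 150, as stated. The article gives no effect size, SD, power or CT:ST ratio, so it cannot be used to size the bias.

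**2. Can the mixture occur?** Yes. Sections 2.2.1, 2.2.2 and 2.3 contain no new-user rule, no washout and no limit on time already treated. The Introduction says that the second-stage pilot has run since November 2017, and section 2.1 dates this study from April 2018. A patient could thus have had up to about five months of collaborative care under that pilot before the study opened. How many such patients there are is not stated.

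**3. When does it bias the contrast?** Suppose CT has no true advantage. Let g be the extra change, in SD units, of new starters over established users, and let p be the share of new starters in each group. Then

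bias = g × (p_CT - p_ST).

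If the shares are equal, the bias is 0 and the type I error stays at 5% whatever g is.

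**4. Illustrative size.** All inputs are assumptions: g = 0.2 to 0.5 SD, a share difference of 0.20 to 0.40, SD of change = 1, and the 120 complete cases split 60/60. The t test then has noncentrality bias / √(1/60 + 1/60) = bias × 5.477, tested two-sided at 0.05.

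| g (SD) | Share difference | Bias (SD) | Noncentrality | False-positive rate |
|---|---|---|---|---|
| any | 0 | 0 | 0 | 5.0% |
| 0.2 | 0.20 | 0.04 | 0.219 | 5.5% |
| 0.2 | 0.40 | 0.08 | 0.438 | 7.2% |
| 0.5 | 0.20 | 0.10 | 0.548 | 8.4% |
| 0.5 | 0.40 | 0.20 | 1.095 | 19.2% |

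**5. Sensitivity to the set-up.** The mixture itself adds variance g²p(1 - p) within a group. Allowing for this in the last row (shares 70% and 30%, normal test) gives 18.7% instead of 19.2%. With a 40/80 split, and the same allowance, it is 17.2%. The 19% needs both assumed extremes at once; at the low end the excess is about half a percentage point.

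**6. Does the stated analysis remove it?** No. The tests in 2.8 condition on nothing. Comparing baseline characteristics could reveal an imbalance in treatment history but would not correct for it.

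**The case against.** The strongest case on the other side has four parts.

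- **The documents do not show the mixing or the imbalance.** A reader might infer that the change scores do in part compare time on treatment. The article does not support that: it permits new and established users but gives no shares, and with equal shares there is no bias. This stands, so the point is conditional.
- **Adding the second system is the exposure.** A reader might argue that imbalance is likely because joining CT is itself a treatment change, and count the response to that change as bias. That fails. Sections 1 and 2.1 ask about collaborative against sole treatment, so the response to adding the second system is part of the CT effect. Only time on treatment before registration can confound.
- **The data may be thinner than they look.** Section 2.4 does not say that treatment history records system, start date or duration, nor that the HIRA data reach back before registration. Table 1 is not shown. This stands as a caution on how finely prior treatment can be coded.
- **Covariates are commonly left to the analysis plan, which is not shown.** This stands in part. The article does not simply omit detail, however: it states the comparison, and what it states is an unadjusted test between self-selected groups. The limitations in section 3 do not mention prior treatment.

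**Conclusion.** The concern holds in conditional form. Eligibility ignores prior treatment, baseline is registration, treatment is freely chosen, and the stated CT-ST comparison is unadjusted. Followed as written, the plan gives a contrast open to confounding by time on treatment before registration. Whether this happens, in which direction and by how much cannot be told from the article. The range of 0.04-0.20 SD and 5.5-19% rests wholly on the assumed early change, the assumed difference in new-starter share and the assumed 60/60 split. It illustrates the risk and does not estimate it. Collecting treatment history is not a fault; the fault is that the stated analysis does not use it.

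**What to change.** In section 2.8, replace the unadjusted comparison of change with a regression of the follow-up score on CT/ST, the baseline score and treatment status at registration. Code that status as none, WM only, KM only or both, with duration where the treatment history or HIRA data give it. Use only information from before registration: a patient on one system who later adds the other becomes CT, so a split on starting or adding a system after registration would nearly reproduce the exposure.

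Tabulate CT/ST by prior-treatment stratum to check overlap. Patients already on both systems at registration would fall almost entirely in CT, so that stratum may hold few or no ST patients and tell little about the contrast. Add a sensitivity analysis that excludes them.

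The cost is analysis-plan wording, a few degrees of freedom, and less precision where overlap is poor. Enrolment and care do not change. Before the wording is fixed, confirm that the case report form records system and duration at registration.
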